#### Anti-nuclear antibodya

#### Alkaline phosphatase isoenzymesa

#### Anti-smooth muscle antibody (or anti-actin antibody)a

Abbreviations: ALT = alanine aminotransferase; AST = aspartate aminotransferase; CPK = creatinine phosphokinase; GGT = gamma-glutamyl transferase; Ig = immunoglobulin; INR = international normalized ratio; RBC = red blood cell; WBC = white blood cell.

a Assayed by Lilly-designated or local laboratory.

b Reflex/confirmation dependent on regulatory requirements and/or testing availability.

## Appendix 5. Blood Sampling Summary

The following tables summarize the approximate number of venipunctures and blood volumes for all blood sampling (screening, safety laboratories, and bioanalytical assays) during the study.

**Protocol J1T-MC-GZEA Sampling Summary**

| Purpose                                | Blood Volume per Sample (mL) | Number of Blood Samples |            | Total Volume (mL) |            |
|----------------------------------------|------------------------------|-------------------------|------------|-------------------|------------|
|                                        |                              | IV Cohorts              | SC Cohorts | IV Cohorts        | SC Cohorts |
| Screening tests a           | 20.5                         | 1                       | 1          | 20.5              | 20.5       |
| Clinical laboratory tests a | 8                            | 9                       | 9          | 72                | 72         |
| Pharmacokinetics                       | 3                            | 10                      | 9          | 30                | 27         |
| Blood discard for cannula patency      | 1                            | 1                       | 0          | 1                 | 0          |
| Pharmacodynamics                       |                              |                         |            |                   |            |
| ApoA-I, apoB, apoC-III                 | 4                            | 11                      | 11         | 44                | 44         |
| Lipid panel b               | 4                            | 11                      | 11         | 44                | 44         |
| ANGPTL 3/8 complex                     | 2.5                          | 9                       | 8          | 22.5              | 20         |
| Immunogenicity                         | 10                           | 4                       | 4          | 40                | 40         |
| Pharmacogenetics                       | 10                           | 1                       | 1          | 10                | 10         |
| Stored serum samples                   | 6                            | 6                       | 6          | 36                | 36         |
| Total                                  |                              |                         |            | 320               | 313.5      |
| Total for clinical purposes            |                              |                         |            | 320               | 320        |

Abbreviations: ANGPTL = angiopoietin-like protein; apo = apolipoprotein; IV = intravenous;

HDL-C = high-density lipoprotein cholesterol; LDL-C = low-density lipoprotein cholesterol; SC = subcutaneous; VLDL-C = very-low-density lipoprotein cholesterol.

a Additional samples may be drawn if needed for safety purposes.

b The lipid panel includes triglycerides, total cholesterol, LDL-C, VLDL-C (calculated), HDL-C, and non-HDL-C (calculated).

---

## **Appendix 6. Protocol Amendment J1T-MC-GZEA(d) Summary**

---

### **A Randomized, Double-Blind, Placebo-Controlled Study to Evaluate the Safety, Tolerability, Pharmacokinetics, and Pharmacodynamics of LY3475766 Overview**

Protocol J1T-MC-GZEA, A Randomized, Double-Blind, Placebo-Controlled Study to Evaluate the Safety, Tolerability, Pharmacokinetics, and Pharmacodynamics of LY3475766, has been amended. The new protocol is indicated by Amendment (d) and will be used to conduct the study in place of any preceding version of the protocol.

This amendment is considered a substantial protocol amendment

The present protocol amendment is intended to change the route of administration in Cohort 5 from IV to SC. The rationale for this change is to enable a better characterization of the duration of pharmacodynamic effects on lipid parameters. The Cohort 5 dose is limited to 600 mg because it requires 6 SC injections given the drug product concentration of 50 mg/mL.

In addition, the maximal number of subjects that can be enrolled in the study was increased from 55 to 70 (Section 5.2) to account for the

1. fact that Cohort 4 needs to be repeated because limited follow-up data are available due to the absence of site visit during multiple weeks around the peak of the COVID-19 pandemic, and
2. potential need to replace subjects from future cohorts in case they are unable to attend site visits due to COVID-19.

The change to performing the complete physical examination either at the screening visit or at check-in/Day -1 was to provide allowance for COVID-19 mitigations depending on local guidance at each CRU.

Finally, changes were made to allow for the possibility of home visits to capture safety and pharmacodynamic parameters in case subjects cannot come to the sites for 1 or several visits, given the pandemic context.

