## **7.2. Method of Treatment Assignment**

Subjects who meet all criteria for enrollment will be randomized to 1 of the study treatment groups on Day 1. Subjects will be randomized in a 3:1 ratio to receive LY3475766 or placebo.

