### Figure GZEA.1. Dose escalation for Protocol J1T-MC-GZEA.

This is a randomized double-blinded SAD design in dyslipidemic but otherwise healthy male and female subjects, investigating the safety, tolerability, PD, and PK of LY3475766 versus placebo.

Subjects will be enrolled in 6 cohorts:

- Cohort 1: 10 mg LY3475766 or placebo IV
- Cohort 2: 30 mg LY3475766 or placebo IV
- Cohort 3: 100 mg LY3475766 or placebo SC
- Cohort 4: 300 mg LY3475766 or placebo SC
- Cohort 5: 600 mg LY3475766 or placebo SC
- Cohort 6: 1000 mg LY3475766 or placebo IV

Doses and the number of cohorts may be adjusted based on ongoing review of the PK, safety, and tolerability data.

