## 7. SAMPLE SIZE JUSTIFICATION

Up to 70 subjects may be enrolled so that 48 subjects (LY3475766: 36, Placebo: 12) have sufficient evaluable data.

The sample size is customary for Phase 1 studies evaluating safety and PK, and is not powered on the basis of statistical hypothesis testing.

Subjects who are randomized and who are discontinued from the study (providing that discontinuation was not as a result of a safety finding) may be replaced to ensure that enough subjects complete the study.

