## 8. DEFINITION OF ANALYSIS POPULATIONS

The “Safety” population will consist of all enrolled subjects who took at least 1 dose of the study medication, whether or not they completed all protocol requirements.

The “Pharmacokinetic” population will consist of all subjects who received at least one dose of LY3475766 and have evaluable postdose PK data.

The “Pharmacodynamic” population will consist of all subjects who received at least one dose of LY3475766 and have evaluable postdose PD data.

All protocol deviations that occur during the study will be considered for their severity/impact and will be taken into consideration when subjects are assigned to analysis populations.

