## **9.5 Safety and Tolerability Assessments**

### **9.5.1 Adverse events**

Where changes in severity are recorded in the Case Report Form (CRF), each separate severity of the adverse event (AE) will be reported in the listings, only the most severe will be used in the summary tables. A pre-existing condition is defined as an AE that starts before the subject has provided written informed consent and is ongoing at consent. A non-treatment emergent AE is defined as an AE which starts after informed consent but prior to dosing. A treatment-emergent AE is defined as an AE which occurs postdose or which is present prior to dosing and becomes more severe postdose.

All AEs will be listed. Treatment-emergent AEs will be summarized by treatment, severity and relationship to the study drug. The frequency (the number of AEs, the number of subjects experiencing an AE and the percentage of subjects experiencing an AE) of treatment-emergent AEs will be summarized by treatment, Medical Dictionary for Regulatory Activities (MedDRA) version 22.0 system organ class and preferred term. The summary and frequency AE tables will be presented for all causalities and those considered related to the study drug. Any serious AEs will be listed.

Discontinuations due to AEs will be listed.

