### 9.5.7 Immunogenicity Assessments

The frequency and percentage of subjects with pre-existing antidrug antibody (ADA) and with treatment-emergent ADAs (TE ADA) to LY3475766 will be tabulated and listed.

For subjects who are ADA negative at baseline, TE ADAs (treatment induced) are defined as those with a titer 2-fold (1 dilution) greater than the minimum required dilution of the assay (1:10). For subjects who are ADA positive at baseline, TE ADAs (treatment boosted) are defined as those with a 4-fold (2 dilution) increase in titer compared to baseline. The frequency and percentage of subjects with cross-reactive and neutralizing antibodies, if measured, may also be tabulated for subjects with TE ADA.

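### The 300 mg SC adverse-event percentage merges the under-followed original Cohort 4 with its repeat, so it may read low, and no planned table would show this

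*Combined protocol and SAP*

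**What the plan says.** - **Why the cohort is repeated.** The overview in protocol Appendix 6 gives the reason: "Cohort 4 needs to be repeated because limited follow-up data are available due to the absence of site visit during multiple weeks". It does not say how many subjects were affected, which visits were missed, or how many weeks were lost.
- **Treatment column.** SAP section 5 defines "Cohort 4: 300 mg LY3475766 or placebo SC". SAP section 6 lists a single 300 mg SC treatment for the tables and pools placebo across cohorts. Neither section separates original from repeat subjects.
- **Denominator.** The Safety population in SAP section 8 is "all enrolled subjects who took at least 1 dose of the study medication, whether or not they completed all protocol requirements".
- **Statistic.** In SAP 9.5.1, "the number of subjects experiencing an AE and the percentage of subjects experiencing an AE) of treatment-emergent AEs will be summarized by treatment". There is no summary of follow-up time and no split of Cohort 4.
- **Missing data.** SAP 13.2 deals only with how listings are displayed.
- **Endpoint.** Protocol section 4 (Table GZEA.1) makes the incidence of AEs and serious AEs a primary endpoint.
- **Size and allocation.** "Up to 70 subjects may be enrolled so that 48 subjects (LY3475766: 36, Placebo: 12) have sufficient evaluable data" (SAP section 7), and "Subjects will be randomized in a 3:1 ratio to receive LY3475766 or placebo" (protocol 7.2).
- **Anti-drug antibodies.** SAP 9.5.7 says: "The frequency and percentage of subjects with pre-existing antidrug antibody (ADA) and with treatment-emergent ADAs (TE ADA) to LY3475766 will be tabulated and listed". It names no denominator.

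**The concern.** A crude percentage over all dosed subjects compares treatments fairly only if they were watched for similar lengths of time. Here the sponsor itself records that one cohort was not. After discharge on Day 8, the Schedule of Activities places SC subjects' laboratory tests on Days 15, 29, 43, 57 and 85 and their ECGs on Days 29 and 85, all at visits. SAP 9.5.5 does not present ECG data and relies on clinically significant findings being reported as AEs, so an ECG that was not taken also removes a possible AE from the table.

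The affected subjects may be about half of the 300 mg SC column but a much smaller share of pooled placebo, so the gap would not cancel in the comparison. A reader who sees a lower rate at 300 mg than at 100 mg and 600 mg could not tell a real difference from less observation. Protocol 10.3.6 uses the accumulated safety data to inform later studies, so the pattern across doses matters even in a descriptive trial.

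**Working it through.** **Step 1: the plan's own figure.** At 3:1, 48 × 3/4 = 36 active and 48 × 1/4 = 12 placebo, as SAP section 7 states. Over six cohorts, 48/6 = 8 per cohort, or 6 active and 2 placebo. No AE rate is stated anywhere, so nothing further can be reproduced.

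**Step 2: who shares the columns.** Assume that the original and the repeat Cohort 4 each have 6 active and 2 placebo subjects. This is an assumption. The rise in the enrolment cap from 55 to 70 adds 15 places, enough for one repeat cohort of 8 with 7 left for replacements, but the documents give no count. The original subjects are then 6/12 = 50% of the 300 mg SC column and 2/14 = 14% of pooled placebo.

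**Step 3: illustrative dilution.** Let p be the true incidence over 84 days (12 weeks), equal in all arms, and f the fraction of that time effectively observed in the original cohort. With a constant hazard:

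- original-cohort incidence: p_o = 1 − (1 − p)^f
- 300 mg SC column: (6p + 6p_o)/12
- pooled placebo: (12p + 2p_o)/14
- other doses: p

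If a share r of the events in the gap is recovered later, take f = [12 − weeks lost × (1 − r)]/12. Four weeks lost with half recovered is then the same as two weeks lost.

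Results for p = 50%:

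| Weeks effectively lost | f | p_o | 300 mg SC | Pooled placebo | Other doses |
|---|---|---|---|---|---|
| 2 (4 lost, half recovered) | 10/12 | 43.9% | 46.9% | 49.1% | 50% |
| 4 (4 lost, none recovered; or 8 lost, half recovered) | 8/12 | 37.0% | 43.5% | 48.1% | 50% |
| 8 (none recovered) | 4/12 | 20.6% | 35.3% | 45.8% | 50% |

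The 300 mg SC column therefore runs from about 35% to 47%. It lies 3 to 15 percentage points below the other doses and 2 to 10.5 points below placebo.

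**Step 4: other rates and the limits.** For p from 10% to 50%, with nothing recovered, the relative fall in the 300 mg SC percentage is 13% to 16% for 4 weeks lost and 29% to 33% for 8 weeks. If all events in the gap are captured later, f = 1 and the bias is zero. If everything after Day 8 were lost (77 days), p = 50% would give 27.8%.

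**Step 5: in subjects.** The range in Step 3 is 12 × (0.500 − 0.469) = 0.4 to 12 × (0.500 − 0.353) = 1.8 subjects out of 12.

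**The case against.** **No document says that AEs in the gap went unrecorded.** What is reported missing is site visits. The Schedule of Activities shows AE reporting as a continuous span, so symptoms could be reported at the next contact. SC subjects were inpatients with telemetry to Day 8. This stands: a reader might infer that the 300 mg rate *is* diluted, but the documents support only that it may be. It does not cover laboratory, ECG or examination findings, which cannot be recalled if nobody looked.

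**The constant hazard is unsupported.** After a single dose, events such as injection-site reactions may cluster in the inpatient week and be fully observed, which would shrink the bias. This also stands, and it is why Step 3 is only an illustration.

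**The shift is small beside the noise.** With 12 subjects at 50%, the binomial standard error is √(0.5 × 0.5/12) = 14 percentage points, and the study "is not powered on the basis of statistical hypothesis testing". True, but in a descriptive study the percentages are themselves the result, and a one-directional error with a known cause can be shown cheaply.

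**Other outputs already help.** All AEs are listed, SAP 9.5.3 and 9.5.4 summarize laboratory and vital-sign data separately, and SAP section 3 allows supplementary analyses. SAP section 8 also lets protocol deviations influence population assignment. These limit the harm. None of them shows the AE percentage by original and repeat cohort, and the deviation clause is generic and gives no rule for Cohort 4. Dose escalation from Cohort 4 rests on data to Day 15 (protocol 7.4.1), so the issue is mainly one of final reporting.

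**Conclusion.** The concern holds in a limited form. The plan merges a cohort with acknowledged limited follow-up with its repeat in a table of a primary endpoint, and gives the reader no way to see the effect. The 300 mg SC AE percentage may be biased downward relative to the other doses and, less so, to placebo. About 35% to 47% in place of 50% is an illustration. It rests on the assumed cohort sizes, a constant hazard, 4 to 8 weeks lost and none to half of the events recovered. With full later capture the bias is zero.

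Two stronger readings are not supported:

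- **That treatment-emergent antibody rates are similarly diluted.** SAP 9.5.7 leaves the denominator open; it does not state an all-dosed rule. Post-dose samples are due on Days 15, 29 and 85 and at early termination. Days 15 to 85 span 70 days, or 63 at the tightest windows (Day 17 to Day 80), so one gap of 28 to 56 days cannot remove all three scheduled samples. Antibody status is also not a listed endpoint.
- **That a rate per attended week would correct the AE table.** Events recalled from unattended weeks would enter the numerator but not the denominator. If events cluster in the inpatient week, the crude percentage is undistorted, while the original cohort's rate would be inflated 12/8 = 1.5-fold to 12/4 = 3-fold.

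**What to change.** In SAP 9.5.1, keep the planned table over all dosed subjects and add:

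1. A supplementary table of treatment-emergent AEs that shows original and repeat Cohort 4 separately, active and placebo, with each group's follow-up duration and number of attended visits.
2. A sensitivity summary that omits the original Cohort 4 subjects from the 300 mg SC and pooled placebo columns.

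As a minor clarification, SAP 9.5.7 should state that percentages for treatment-emergent antibodies use subjects with a baseline and at least one post-dose antibody result.

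The cost is a few lines of SAP text, one extra table and one sensitivity summary, with no new data. The drawback is small numbers: on the assumed sizes, 6 active and 2 placebo subjects in each part of the split. It should therefore be read descriptively beside the all-dosed table.

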## Revised Protocol Sections

**Note:** All deletions have been identified by ~~strikethroughs~~.  
All additions have been identified by the use of underscore.

### 1. Protocol Synopsis

#### Number of Subjects:

Up to ~~5570~~ subjects may be enrolled so that 48 subjects (LY3475766: 36, Placebo: 12) have sufficient evaluable data.

### 2. Schedule of Activities

#### Study Schedule Protocol J1T-MC-GZEA

| Procedure                     | Screening         |    | Treatment Period |   |   |   |   |   |   |        |        |        |        |        |        | Follow-up | E T | Notes                                                                                                    |
|-------------------------------|-------------------|----|------------------|---|---|---|---|---|---|--------|--------|--------|--------|--------|--------|-----------|-----|----------------------------------------------------------------------------------------------------------|
|                               |                   |    | Week 1           |   |   |   |   |   |   | Week 2 | Week 3 | Week 4 | Week 5 | Week 7 | Week 9 | Week 13   |     |                                                                                                          |
| Day                           | Day -28 to Day -2 | -1 | 1                | 2 | 3 | 4 | 5 | 6 | 7 | 8      | 15 ±2  | 22 ±2  | 29 ±2  | 43 ±5  | 57 ±5  | 85 ±5     |     |                                                                                                          |
| Complete physical examination | X                 |    |                  |   |   |   |   |   |   |        |        |        |        |        |        |           |     | Complete examination (except genital and rectal). Can be completed at either Screening or Day -1. |

### 3.3 Benefit/Risk Assessment

LY3475766 has not been administered to humans. The nonclinical safety information for LY3475766 supports the transition from preclinical status to clinical development. Based on the mechanism of action and nonclinical data, LY3475766 is not considered to be a high uncertainty compound. The only potential risk that is anticipated relates to the finding of a nondose-dependent decrease in heart rate in a 1-month Good Laboratory Practice toxicology study that was performed in cynomolgus monkeys; there were no adverse events (AEs) or any significant electrocardiogram (ECG) findings associated with the decrease in heart rate. Refer to the IB for LY3475766 for more details. This risk is considered to be monitorable and manageable at the planned doses of 10 mg, 30 mg, ~~450 mg~~, and 1000 mg IV and 100 mg, 300 mg, and 600 mg SC for LY3475766 in dyslipidemic but otherwise healthy subjects.

### 5.1. Overall Design

[figure not shown]

**Figure GZEA.1. Dose escalation for Protocol J1T-MC-GZEA**

Potential subjects will be screened to assess their eligibility to enter the study within 28 days prior to Day 1. In case of safety concerns, participants may be required to stay at the clinical site for a longer period at the discretion of the investigator. Subjects in the IV cohorts will be confined at the CRU from Day -1 (the day before dosing) to Day 4 (72 hours postdose) but will return to the CRU on Day 8 for an outpatient visit. Subjects in the SC cohorts will be confined at the CRU from Day -1 (the day before dosing) to Day 8 (168 hours postdose). Subjects in all cohorts will return to the clinical research unit (CRU) as outpatients at predetermined visits for up to approximately 84 days postdose for follow-up assessments. In case a subject cannot come to the site for 1 or several outpatient visits, home visits may potentially be performed instead, depending on the circumstances and if agreed upon between investigator and sponsor.

Subjects will be confined at the CRU:

- from Day -1 (the day before dosing) to Day 4 (72 hours postdose) for IV cohorts, and
- from Day -1 (the day before dosing) to Day 8 (168 hours postdose) for SC cohorts.

This is a randomized double-blinded SAD study in dyslipidemic but otherwise healthy male and female subjects investigating the safety, tolerability, PD, and PK of LY3475766 versus placebo.

Subjects will be enrolled in 6 cohorts:

- Cohort 1: 10 mg LY3475766 or placebo IV
- Cohort 2: 30 mg LY3475766 or placebo IV
- Cohort 3: 100 mg LY3475766 or placebo SC
- Cohort 4: 300 mg LY3475766 or placebo SC
- Cohort 5: 600 mg LY3475766 or placebo ~~IV~~-SC
- Cohort 6: 1000 mg LY3475766 or placebo IV

Potential subjects will be screened to assess their eligibility to enter the study within 28 days prior to Day 1. In case of safety concerns, participants may be required to stay at the clinical site for a longer period at the discretion of the investigator. Subjects in the IV cohorts will be confined at the CRU from Day 1 (the day before dosing) to Day 4 (72 hours postdose) but will return to the CRU on Day 8 for an outpatient visit. Subjects in the SC cohorts will be confined at the CRU from Day 1 (the day before dosing) to Day 8 (168 hours postdose). Subjects in all cohorts will return to the clinical research unit (CRU) as outpatients at predetermined visits for up to approximately 84 days postdose for follow-up assessments.

